### Data collection and management

#### Collection of information at T1

T1 data collection will be conducted by the RA, a master’s level researcher trained by the PI in the administration of scoring of the three assessments to be administered. The RA will administer the GAI. The GAI has been validated for use in community dwelling adults over the age of 60, with excellent test-retest reliability of *r* = .91 to .95 [35, 53–55]. This anxiety scale was selected because it is commonly used in a range of clinical settings [56]. The RA will administer the PSQI and the MMQ [46, 57]. The PQSI is a sleep quality and sleep disturbance assessment validated for use with community dwelling older adults [46]. This measure was selected because sleep complaints are frequently associated with anxiety [58]. The PQSI is a simple 19 item subjective measure of sleep quality and patterns of sleep using a 0 to 3 Likert scale [59]. The PQSI has been demonstrated to have excellent test-retest reliability (*r* = .85–.87) and internal consistency of Cronbach’s *a* of .80–.83 [46, 60, 61]. The MMQ is a 21-item brief self-report assessment of subjective memory ability validated for use with community dwelling older adults [57, 62]. This assessment measures satisfaction, ability and strategy use in memory. It was chosen because older adults with anxiety frequently report problems with memory [4, 5, 15–17]. The MMQ has high test-retest reliability over time (.86–.95) [62, 63]. Cronbach’s *a* internal consistency is good at .87 to .93 [57, 62, 64].

#### Collection of information at T2

All participants will be contacted by telephone by the RA to re-administer the GAI, PSQI, and MMSQ within 1 week of completion of the intervention.

#### Collection of information at T3

All participants will be contacted by telephone by the RA to re-administer the GAI, PSQI, and MMSQ and to collect data on extraneous life events, within 1 week of completion of the intervention for the wait list control group. The RA will attempt to collect data from all participants whether or not all sessions are attended.

### Feasibility and acceptability outcomes

Feasibility and acceptability outcomes will be determined by the following: recruitment and enrollment will be considered feasible if 70% of the total number of potential participants meeting eligibility requirements consent to enroll [44], and if 48 participants can be enrolled within a 3-month period (16 participants recruited per month). As a dropout rate of 35% is consistent with MBIs based in self-management and with a technology based delivery, a retention rate of 65% will be used to determine feasibility [65, 66]. Participants’ adherence to all components of the intervention will be defined by attendance of 6/8 sessions and participation in meditation, journaling, and reporting during the sessions, as observed and documented by the PI. In the tradition of MBI research, the intervention will be considered complete if participants are able to attend a minimum of 6/8 meetings [45]. It will be assumed that participants will be honest about meditation within the group, although direct evidence can only be inferred through observation [67]. Participants are not required to practice at home; however, they will be asked to self-report on the frequency and duration of home practice meditation and journaling to explore whether there is a relationship to outcomes.

### Treatment fidelity

The PI received training and certification in a joint program with the University of Toronto, Faculty of Medicine, and Mt. Sinai Hospital, Toronto, Canada.

### Participant retention

The PI will encourage participant retention by sending reminder emails of group start dates to wait listed participants at 4 weeks, 2 weeks, and 1 week prior to the beginning of the group.

### Statistical methods

Data entry will be conducted by the RA. Data analysis will be conducted by the PI at the end of the study using SPSS V27 [68]. All data will be examined by running frequencies on each variable to determine if values are missing or out of range. Possible errors will be compared to raw data and corrected as necessary to ensure accuracy [67]. As is recommended for pilot feasibility studies, the following descriptive statistics will be used: for continuous variables, minimum, maximum, mean, median, mode standard deviation, skewness, and kurtosis; if continuous variables are skewed, non-parametric descriptive statistics will be reported; for categorical variables, frequencies will be used [69, 70]. Graphical displays such as histograms or boxplots will be presented to demonstrate and better understand the central tendency and dispersion of the data [67]. Recruitment, enrollment, and retention rates will be calculated. Rates of attendance and adherence to each component of the intervention will also be calculated to determine acceptability.

To examine whether there have been potential changes in the secondary outcomes, descriptive statistics will be used to analyze and present demographic and baseline data. Categorical and ordinal data will be compared using chi-square. Continuous data will be compared using a *t*-test. The mean change in the intervention group and wait list control group outcomes will be compared post intervention (T3) using an independent samples *t*-test, and Cohen’s *d* will be calculated for effect size [67]. Data from each of the groups will be combined to form a larger sample size to evaluate the effect of the intervention. Analysis of pooled data will be conducted using a paired sample *t*-test and Cohen’s *d* to examine the intervention effect over baseline measures. Change over time for the intervention group from T1 to T2 to T3 will be calculated by using repeated measures ANOVA to determine if change has occurred and/or is maintained in the intervention group.

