### Objectives

Primary objectives are as follows:
Determine if participants can be recruited, enrolled, and retainedDetermine if participants can adhere to all components of the intervention

Secondary objectives are as follows:
Examine the extent to which participants who receive the intervention have decreased levels of anxiety compared to those who do not receive the interventionExamine the extent to which participants have improved sleep quality compared to those who do not receive the interventionExamine the extent to which participants who receive the intervention have improved subjective memory functioning compared to those who do not receive the intervention

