### Design and setting

The study is a feasibility randomized controlled trial (RCT) using a wait list control trial design. Due to COVID-19 restrictions, this study has been adapted from in-person delivery to telehealth delivery via Zoom. The first 48 people to meet the eligibility criteria will be randomly allocated to receive EFMT immediately, or in 8 weeks from time of baseline assessment (1:1 allocation ratio). Data will be collected by a blinded to group research assistant (RA) at baseline (T1), 8 weeks following baseline (T2), and 16 weeks following baseline (T3). Participants will be recruited from primary care clinics and community organizations that provide support to older adults. The principal investigator (PI)/facilitator of the EFMT groups will be blinded to the results of outcome assessments until the end of the intervention phase of the study. The PI is a registered psychotherapist certified in delivering EFMT and will facilitate all groups.

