### Interventions

#### Comparators

The comparator will be no treatment (treatment as usual) for the controlled wait list group. All participants will receive the intervention. All participants will receive T1, T2, and T3 assessments within 7–10 days of each timepoint.

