#### Intervention description

EFMT is a group intervention traditionally consisting of eight weekly in-person group meetings of 2.5 h, with group sizes of between 10 and 12 participants. Due to COVID-19 restrictions, EFMT will be delivered by Zoom to groups of six participants and weekly meetings will be shortened to 1.5 h to reduce Zoom fatigue, a phenomenon noted in popular media [40, 41]. For modification to video-delivery of the intervention, the number of participants has been decreased from 10 to 12, to six to provide adequate time for all components of the intervention to be delivered. Each group meeting consists of a check-in period of 5 min, the reading of meditation instructions by the PI, 20 min of silent unguided meditation, 5–10 min of journaling about what arose for participants during the meditation, and a 5-min break. After journaling, each participant takes a turn and describes their meditation experience, with the PI offering empathic exploration. In emotion-focused mindfulness therapy, as in emotion-focused therapy, empathic exploration is a core competency that involves reflection, validation, responding to participants, and heightening their emotional experience [42, 43]. This is the process that is the heart of change and encourages participants to become more familiar with, and develop a tolerance to, distressing emotions [33].

EFMT poses little risk for participants. Meditation can sometimes cause uncomfortable feelings to arise when participants connect with emotions. Participants may decide to withdraw from the intervention if overwhelming emotions emerge. Participants may decline to answer questions during the reporting part of the meditation group. Should a participant become upset during any part of the group, the PI can: ask that participant to remain after the group to talk; ask that group participants take a short break while the PI speaks with the upset participant; lead the upset participant through a relaxation and grounding exercise; ask the participant if the PI may contact someone of their choice for support; and help the upset participant to access counseling. Participants may withdraw from the study at any time; however, study participants will be retained in the trial wherever possible to enable follow-up data collection and prevent missing data.

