### Outcome collection and measures

*Aim 1*. Determine if participants can be recruited, enrolled and retained

Recruitment, enrollment and retention data will be used to evaluate feasibility. Data will be gathered and measured on the number of potential participants referred and screened for eligibility, participants meeting eligibility requirements, participants enrolled, and participants completing the intervention. Recruitment and enrollment will be considered feasible if 70% of the total number of potential participants meeting eligibility requirements consent to enroll [44], and if 48 participants can be enrolled within a 3-month period (16 participants recruited per month). Retention will be considered feasible if 65% of participants complete data collection at both timepoints [45].Variables such as changes to medications, beginning, or stopping mental health counseling and significant life events will be tracked by the RA at T3 data collection timepoint. Extraneous variables will be important to gather to identify other potential reasons for changes to secondary outcomes aside from EFMT.

*Aim 2*. To determine if participants can adhere to all components of the intervention

Adherence will be used to measure acceptability. The intervention will be considered acceptable if 70% of participants attend of a minimum of six meetings [44]. As well, acceptability for measures of adherence to meditation, journaling, and reporting will be gathered through PI observation and documentation. Adherence to these components will be considered acceptable if the majority (75% or more) of participants appear to be meditating, journaling and actively report their meditations. Participants will not be required to practice between meetings; however, data will be gathered on the frequency and duration of home practice meditation and journaling to explore whether there is a relationship to outcomes. Participants will complete weekly reporting forms to be emailed to the PI. The PI will keep an observational diary noting what works well and perceived areas of challenge.

*Aim 3*. To determine the secondary objective of whether participants who receive the intervention potentially have decreased levels of anxiety compared to those participants who do not receive the intervention, the GAI will be used [35]. Outcome measures will be collected using the GAI at T1, T2 and T3.

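### The only between-arm test of post-baseline outcomes is set at T3, when the wait list arm has also had EFMT, so it cannot compare treated with untreated participants

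*Protocol article*

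**What the plan says.** - **Objectives:** the anxiety objective is whether participants given the intervention "have decreased levels of anxiety compared to those who do not receive" it. The sleep and memory objectives use the same comparator.
- **Comparators:** "The comparator will be no treatment (treatment as usual) for the controlled wait list group". The same paragraph adds: "All participants will receive the intervention".
- **Design and setting:** participants are "randomly allocated to receive EFMT immediately, or in 8 weeks from time of baseline assessment (1:1 allocation ratio"). Assessments are at baseline (T1), week 8 (T2) and week 16 (T3).
- **Intervention description:** "EFMT is a group intervention traditionally consisting of eight weekly in-person group meetings of 2.5 h". The Zoom version has shorter meetings and smaller groups but is still an eight-week programme (Eligibility criteria) of eight sessions (Feasibility and acceptability outcomes).
- **Collection of information at T3:** the T3 call is made within one week of "completion of the intervention for the wait list control group".
- **Statistical methods:** "The mean change in the intervention group and wait list control group outcomes will be compared post intervention (T3"), by independent samples t-test with Cohen's d. The section adds a paired t-test on the two arms pooled, and a repeated measures ANOVA over T1, T2 and T3 in the intervention group alone.
- **Outcome collection and measures:** changes in medication and counselling and "significant life events will be tracked by the RA at T3 data collection timepoint". The section on T2 collection lists no such questions.

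**The concern.** A wait list design gives a randomised comparison with no treatment only while the control arm is still waiting. Here that period ends at about week 8. The plan places its between-arm test eight weeks later, when no untreated group remains. The test then compares participants treated about eight weeks earlier with participants who have just finished.

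That is a question about durability or timing, not about EFMT versus nothing. An effective treatment whose benefit lasts would give an expected difference of zero. One whose benefit fades would appear worse in the immediate arm. The Discussion says the findings will inform sample size calculations for a definitive trial, and this contrast is the one between-arm comparison for which the plan calculates an effect size.

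**Working it through.** **Exposure at each visit** (from Design and setting, Comparators, Fig. 1 caption and Collection of information at T3):

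| Visit | Immediate arm | Wait list arm | Between-arm outcome test planned? |
|---|---|---|---|
| T1, week 0 | untreated | untreated | baseline description only |
| T2, week 8 | just treated | untreated | none |
| T3, week 16 | treated about 8 weeks earlier | just treated | yes |

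T2 is the only post-baseline visit with an untreated comparator. The Fig. 1 caption confirms that T2 is collected in all participants at the end of the first intervention period.

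**Do the other analyses fill the gap?** The pooled paired t-test is a before-and-after comparison with no concurrent control. The ANOVA uses one arm. The general chi-square and t-test sentences follow a sentence about demographic and baseline data and name no later visit. None gives a treated-versus-untreated contrast.

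**The plan's own figure.** Sample size: 4 blocks × 12 = 48, and 4 × 6 = 24 per arm. This reproduces. It was set by group logistics. The protocol gives no effect size, SD, alpha or power, so everything below is illustrative.

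**Expected contrast.** Let d be the benefit at the end of a course, in SD units, and m the share kept eight weeks later. Positive values favour the immediate arm.

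- T2: d − 0 = d
- T3: m·d − d = (m − 1)d

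| Assumed m | T3 contrast, d = 0.5 (T2 = 0.50) | T3 contrast, d = 0.6 (T2 = 0.60) |
|---|---|---|
| 1.25 (continued gain) | +0.125 | +0.15 |
| 1.0 (fully maintained) | 0 | 0 |
| 0.7 | −0.15 | −0.18 |
| 0.5 | −0.25 | −0.30 |

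**What the T2 contrast could show.** Assume d = 0.6, within-person correlation ρ = 0.6, 24 per arm and two-sided alpha 0.05.

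- SD of change = √(2(1 − ρ)) = √0.8 = 0.894
- Standardised effect on change = 0.6/0.894 = 0.671
- Noncentrality = 0.671 × √(24/2) = 2.32
- Power = 62%

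A simulation of 20,000 trials on these assumptions gives the same 62% at T2. At T3 with full maintenance, the test favours the immediate arm in 2.6% of trials. That is chance: a two-sided 5% test rejects about 2.5% of the time in each direction when the true difference is zero.

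The 62% depends on the assumptions. It is 46% at ρ = 0.4 and 90% at ρ = 0.8. With 16 per arm (24 × 0.65 = 15.6, the protocol's retention threshold) and ρ = 0.6 it is 45%. The (m − 1)d result depends on neither ρ nor sample size.

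**The case against.** **These outcomes are secondary and unpowered.** The protocol says so, and its Discussion disclaims hypothesis testing. The feasibility and acceptability criteria do not depend on this test. All of that stands. But low power makes an estimate imprecise, whereas this analysis estimates a different quantity, which more participants would not cure.

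**T3 may be a slip for T2.** This is plausible: the Fig. 1 caption labels both visits post-intervention, and the design makes little sense without a T2 contrast. The text nevertheless names T3 and has to be corrected either way. Nor does it say where the change starts. Measuring each arm's change over its own treatment period would not help, because that also compares treated with treated.

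**The abstract and the opening of Methods also describe the secondary outcomes as change over time.** The pooled test and the ANOVA address that, but without a control. The Objectives section asks for a controlled comparison.

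**A T3 effect size is not always null or reversed.** Correct. If benefit keeps growing after the course (m above 1), T3 favours the immediate arm. It would still not estimate d unless m happened to equal 2. That this d would be used for planning is an inference from the Discussion, not a statement in it.

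**Asking about medication, counselling and life events only at T3 is a separate and lesser matter.** This is fair. The questions are not shown and may ask for dates. The main conclusion does not rest on it.

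**Conclusion.** The concern holds. As written, the plan has no analysis that answers its treated-versus-untreated secondary objectives, and its one between-arm outcome test measures maintenance or timing instead. This follows from the protocol's own timeline and needs no numerical assumption.

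The size does rest on assumptions. For an effect of 0.6 SD, T2 would estimate 0.60. T3 would estimate zero under full maintenance, or 0.18 to 0.30 SD in favour of the wait list arm if 70% to 50% is maintained. The sample size of 48 and the primary feasibility objectives are unaffected. Because the stated analysis is wrong for its objective and not merely unspecified, it must be fixed.

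**What to change.** 1. In Statistical methods, make the between-arm comparison of GAI, PSQI and MMQ the T1-to-T2 change, immediate arm versus wait list arm, and calculate Cohen's d there. Report it as an estimate with a confidence interval. On the raw-score SD scale and a normal approximation, the 95% half-width for a difference in means is about 1.96 × √(2/24) = 0.57 SD with 24 per arm and 1.96 × √(2/16) = 0.69 SD with 16.
2. Keep T3 for maintenance in the immediate arm and for post-treatment description in the wait list arm. Label the pooled before-and-after analysis as uncontrolled.
3. As a minor addition, ask the medication, counselling and life-event questions at the T2 call as well as at T3.

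The first two changes are edits to the text. They need no new outcome data, and N stays at 48. The third adds one question set to an existing call. It slightly raises the chance that a participant reveals allocation, a risk the Blinding section already notes for T2, so these questions should come last.

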### Eligibility criteria

The PI will screen potential participants for the following inclusion criteria: participants will be community dwelling older adults 55 years of age and older with no existing therapeutic alliance with the PI; will self-report or have a diagnosis of anxiety; can speak English; and can commit to the 8-week program and three assessment phone calls with the RA. The presence of symptoms of anxiety will be assessed using the Geriatric Anxiety Inventory (GAI) with a cut off score of 10 which indicates the presence of anxiety [35]. Exclusion criteria will be having begun or stopped psychotropic medications within the previous six weeks [36]. Further exclusion criteria will be a Telephone Montreal Cognitive Assessment (T-MoCA) with a cut off score of 19 which indicates the possibility of mild cognitive impairment and would be beyond the scope of this study [37, 38]. The T-MoCA is conducted by telephone and, due to COVID-19 restrictions, will be administered by the PI by telephone, who has been certified in the administration and scoring of the MoCA. Potential participants will be considered eligible to participate in the study if: their GAI score is ≤ 10; and their T-MoCA score is ≤ 19 [37, 38]. The T-MoCA is conducted by telephone and is a validated version of the MoCA that assesses phonemic fluency; word recall and orientation to day, date, and location; and does not use items that require paper and pencil or animal identification [38, 39]. The T-MoCA is demonstrated to be accurate in detecting mild cognitive impairment (95% confidence interval) with excellent test-retest reliability and internal consistency [38, 39].

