## Discussion

A potential limitation to this trial is that it is not powered to examine effectiveness and findings will not be generalizable to other populations. However, findings will inform planning of a definitive RCT including anticipated time required for recruitment, strategies to promote adherence, and sample size calculations. This study will not examine hypothesis testing based on the CONSORT extension. Due to COVID-19, this group has been modified for delivery in an online format to ensure the participants’ safety. This trial will provide unique information to international researchers and clinicians regarding a novel treatment for late-life anxiety and will become the first RCT to determine the feasibility of EFMT for older adults with late-life anxiety.

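### The pooled paired analysis labels uncontrolled before-after change as the effect of EFMT, and using T2 as the wait list's pre-score reduces this bias without removing it

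*Protocol article*

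**What the plan says.** Participants are "randomly allocated to receive EFMT immediately, or in 8 weeks from time of baseline assessment (1:1 allocation ratio"), with assessments "at baseline (T1), 8 weeks following baseline (T2), and 16 weeks following baseline (T3"). The Comparators section adds: "All participants will receive the intervention". The T3 assessment falls "within 1 week of completion of the intervention for the wait list control group". The immediate arm is therefore treated during T1-T2 and the wait list during T2-T3, and the only untreated comparator is the wait list between T1 and T2.

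The Statistical methods section plans three analyses of change in the secondary outcomes:

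- an independent-samples t-test of mean change between arms, labelled T3;
- a pooled analysis, described as "Data from each of the groups will be combined to form a larger sample size to evaluate the effect of the intervention", using a paired t-test and Cohen's d "to examine the intervention effect over baseline measures";
- a repeated measures ANOVA in the intervention group alone.

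The Objectives section frames each secondary objective as a comparison with people who do not receive EFMT. The Discussion states that "findings will inform planning of a definitive RCT including anticipated time required for recruitment, strategies to promote adherence, and sample size calculations".

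**The concern.** A paired test asks only whether scores moved between two visits. Reading the movement as the effect of EFMT assumes that nothing else moved them. The trial gives reasons for doubt: it runs during COVID-19 restrictions, the same scales are repeated by telephone, and people enter because of reported anxiety. The section on outcome collection itself accepts that outcomes may change for reasons other than EFMT, but it only records such events at T3 and names no adjustment for them.

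The other two planned analyses do not fill the gap. By T3 the wait list has also had EFMT, and the ANOVA has no comparator. As labelled, no planned analysis of change cleanly sets treated weeks against untreated weeks.

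At stake is the effect estimate with the largest sample in the plan. It could look encouraging with no EFMT effect, in a study whose findings are meant to inform a definitive trial.

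**Working it through.** **Inputs from the protocol article.** Four blocks of 12 give 4 × 12 = 48 participants, and 48/2 = 24 per arm, which reproduces the stated sample size. The retention benchmark of 65% gives 0.65 × 48 ≈ 31. No alpha, SD, between-visit correlation or expected drift is stated, so there is no power figure to reproduce.

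**Assumptions made here.** Two-sided 5% level; equal SD at each visit; equal correlation r between visits, 0.5 or 0.7; independent participants; shared drift in SD units.

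**Step 1: what the pooled mean estimates.** Let θ be the EFMT effect, d1 the shared change over T1-T2 and d2 the shared change over T2-T3.

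- Immediate arm, T1 to T2: θ + d1.
- Wait list, T2 to T3: θ + d2.
- Wait list, T1 to T3: θ + d1 + d2.

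With equal arms, the pooled mean is:

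- wait list pre-score at T2: θ + (d1 + d2)/2;
- wait list pre-score at T1, the visit the plan calls baseline: θ + d1 + d2/2.

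| Shared change (SD) | Bias, pre-score T1 | Bias, pre-score T2 |
|---|---|---|
| d1 = d2 = 0.2 | 0.30 | 0.20 |
| d1 = d2 = 0.3 | 0.45 | 0.30 |
| d1 = 0.5, d2 = 0 | 0.50 | 0.25 |

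Using T2 lowers the bias in each row but does not make it zero.

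**Step 2: false positives with θ = 0, equal drift c and pre-score T2.** The standardised paired change is dz = c/√(2(1 − r)) and the noncentrality is dz√n. For c = 0.2 and r = 0.5, dz = 0.2/√1 = 0.200 and the noncentrality is 0.200 × √48 = 1.39. The exact noncentral t gives:

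| c (SD per 8 weeks) | r | dz | Rejection, n = 48 | Rejection, n = 31 |
|---|---|---|---|---|
| 0.1 | 0.5 | 0.100 | 10% | 8% |
| 0.1 | 0.7 | 0.129 | 14% | 11% |
| 0.2 | 0.5 | 0.200 | 27% | 19% |
| 0.2 | 0.7 | 0.258 | 42% | 29% |
| 0.3 | 0.5 | 0.300 | 53% | 37% |
| 0.3 | 0.7 | 0.387 | 75% | 55% |

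Simulation (4,000 trials per setting) agrees at c = 0.2 and 0.3. It also gives 38% (r = 0.5) and 57% (r = 0.7) when the drift is 0.5 SD in T1-T2 only. With a T1 pre-score and c = 0.2, it gives 52% and 75%.

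**Step 3: the randomised contrast.** Immediate minus wait list over T1-T2 is (θ + d1) − d1 = θ. With θ = 0 and 24 per arm, its simulated rejection rate was 4.2% to 5.5% across all the drifts and correlations tried.

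**Step 4: a conditional sizing illustration.** Suppose the true between-arm difference is 0.3 SD and a later trial is sized for 80% power on the pooled value 0.3 + c, with both on the change-score scale so that r cancels. True power is then approximately Φ(2.80 × 0.3/(0.3 + c) − 1.96). At c = 0.1, 0.2 and 0.3 this is about 56%, 39% and 29%.

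**The case against.** **This is a pilot.** The protocol says that it is not powered for the secondary outcomes and disclaims hypothesis testing. That lowers the weight of the rejection rates. It does not answer the bias, which enters Cohen's d with or without a p-value.

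**The size of the drift is assumed.** This stands. Constant drift is a convenience: change confined to one window enters at half size under a T2 pre-score, and opposite drifts would partly cancel.

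**Regression to the mean.** A reader might infer that selection on the GAI must produce apparent improvement. The documents do not support that. The Eligibility criteria section gives a "cut off score of 10 which indicates the presence of anxiety", yet later makes people eligible at scores of 10 or below. The expected direction of regression depends on which statement governs, and the two must be reconciled. Screening by the PI also appears to be separate from the research assistant's T1 assessment, so some or all of the regression could occur before T1. The PSQI and MMQ are not selection variables. Repeat testing and pandemic-period change do not depend on the GAI rule.

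**The definitive trial.** A reader might infer that it will be undersized. The Discussion says only that findings will inform sample size calculations. It does not name the pooled d, and the between-arm test has its own d, although that test is labelled T3. Step 4 shows what would follow if the pooled d were used, not what is planned.

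**Conclusion.** The point holds as a fault in interpretation that the article itself fixes: data, method and causal label are all stated. The pooled result is the EFMT effect plus (d1 + d2)/2, or plus d1 + d2/2 with T1 as the wait list's pre-score. Choosing T2 reduces the bias but does not remove it.

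The algebra needs only equal arms and change shared by both. The 10% to 75% range rests on the assumed drift, correlation and alpha, and it shows sensitivity rather than forecasting this trial. The documents do not establish that the bias favours EFMT. The matter is worth correcting because the label conflicts with the trial's own comparative objectives and the data for a controlled estimate are already being collected. It concerns secondary outcomes only.

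**What to change.** 1. **Statistical methods, pooled analysis.** Report the paired result and its d, with a confidence interval, as uncontrolled within-person change during EFMT, and not as the intervention effect.
2. **Statistical methods, effect estimate.** Take it from the randomised between-arm contrast of T1-T2 change, the only period with an untreated comparator.
3. **If an estimate using both arms' treated data is also wanted.** Present it as secondary, from a mixed model with participant, visit and treated/untreated terms. State how the immediate arm's T3 is coded; coding it as treated assumes that the effect persists unchanged after the sessions end. Subtracting the wait list's T1-T2 change from the pooled treated change is not a substitute. It estimates θ + (d2 − d1)/2, so with d1 = 0.5 and d2 = 0 its bias is −0.25 SD.
4. **Discussion.** State that sample size calculations for the definitive trial will not use the pooled before-after d.

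**Cost.** The change is to wording and analysis only, with no new data. The interval is wider: under the assumptions above, the standard error of the contrast relative to the pooled change is √((2/24)/(1/48)) = 2, so the interval is about twice as wide. The effect estimate will probably be smaller.
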